**Figure 2 F2:**
[figure not shown]
Flowchart of the pediatric exacerbation study network. Study design is characterized by baseline, first and second FU visits. At each study visit, different biomaterials and clinical item parameters will be obtained.

In detail, at baseline and second FU visits, serum and plasma samples will be collected in monovettes purchased from Sarstedt®. Serum samples will be kept in the dark for 20 min before centrifugation. Plasma samples will be centrifuged upon collection (2.000×g for 15 min). Two-hundred microliter supernatant (serum/plasma) will be transferred to cryotubes, and the samples will be stored at −80°C until experimental use. Furthermore, the blood collection during both visits comprises also PBMC collection. Lithium-heparin/ethylenediaminetetraacetic acid blood tubes (Sarstedt, ORT) will be filled up with blood. The blood volume will be diluted with phosphate-buffered saline (Biochrom, ORT) and overloaded on Biocoll (Biochrom, ORT) in an appropriate ratio, as described in the literature. Afterward, centrifugation at 300 × g for 30 min will be taken place. Carefully, the PBMCs will be aspirated and transferred to a new column tube, and after several phosphate-buffered saline washing steps and cell calculating, the PBMCs will be diluted in fetal bovine serum, dimethyl sulfoxid (and DMEM) in an appropriate ratio as described in the literature and stored until experimental use. In addition, the nasal and pharyngeal swabs will be directly stored at −80°C until microbiome and fungiome analyses. The microbiome project is still under publication elsewhere. The methods will be shortly presented here. After DNA isolation of the swabs, a previously established protocol for 16S- and 18S-rRNA will be used. Region-specific primers will be chosen, and the region-of-interest will be transcribed and amplified through PCR steps. Finally, a barcode will be adapted to the amplified template and via NGS, the microbiome and fungiome libraries will be bioinformatically analyzed and correlated to the clinical item parameters. The microbiome project is still under publication elsewhere, and the fungiome project is currently in the establishing stage. The fungal sequencing steps will be adapted as published by Illumina® (https://emea.illumina.com/content/dam/illumina-marketing/documents/products/appnotes/its-metagenomics-app-note-1270-2018-001-web.pdf).

Moreover, through a brushing procedure, nasal epithelial cells will be isolated and used for functional analyses. For this, different cell culture models (2D submerged, organotypic 3D cell culture, and organoid models) will be established. These cell culture models will enable us to perform *in vitro* analyses of *in vivo* observed results derived from the entire study population, i.e., describing signaling pathways or evaluation of biomarkers. Moreover, induced sputum will be analyzed for cytokine and chemokine analyses. Furthermore, a questionnaire will be filled by subjects and custodians and a lung function test (including body plethysmography, spirometry, and exhaled NO for children beyond 5 years of age) will be performed at baseline and second FU visits. In addition, subjects (>2 years of age) will perform an impulse oscillometry. The questionnaire comprises different questions on the history of the child and the custodians, current clinics, including asthma scoring systems (Table 1). This questionnaire was based on a specific patient-related anamnesis questionnaire used in our clinics for many years when examining patients with respiratory symptoms. It was not necessary to validate the questions. The item parameters are sufficient enough to characterize the study population in different clinical phenotypes.

**Table 1 T1:** Questionnaire used for the entire study population, not validated or published before, previously established, and currently still in use in the clinical routine.

**Questionnaire (summarized item parameters)**
i. Age and sex at study enrollment
ii. Place of birth, mode of birth, gestational weeks, birth height and weight
iii. Postnatal complications, including infections, mechanical ventilation
iv. Duration of breastfeeding
v. Vaccination
vi. Pet owner
vii. Allergic symptoms including itch, rhinitis, conjunctivitis, and duration of allergic symptoms
viii. Atopic eczema
ix. Family history for atopic disorders
x. Recurrent respiratory symptoms at preschool period
xi. Chronic medication and the response to this medication
xii. Asthma control test score
xiii. Current symptoms (e.g., cough, chest tightness, wheezing, and fever)

The study recruitment started in January 2018 and will be finished on 31/12/2021. All patients with typical symptoms requiring study enrollment will be presented at the emergency room of the (affiliated) university children's hospitals, and a study enrollment protocol will be obtained. Participating study centers are Center of Child and Adolescent Medicine, Helios University Hospital Wuppertal of Witten/Herdecke University, Germany and Children's Hospital, and Helios Hospital Niederberg, teaching hospital of University Hospital Essen/Germany. All participated subjects and/or their parents/legal guardians provided written informed consent. Healthy controls will be recruited mostly from children of teammates of the study centers, or the following alternatives may be considered for the recruitment of healthy children and adolescents, e.g., calls in social platforms, flyers for day-care centers, schools, private practices, social institutions, newspapers, and internet. These announcements will be separately reported to the ethics committees in advance.

A patient stratification in subgroups (atopic vs. non-atopic, transient vs. seasonal-dependent vs. multi-triggered vs. single-triggered vs. permanent wheezers, steroid-independent or steroid-dependent phenotypes) were based on clinical (questionnaire) and laboratory parameters (e.g., immunoglobulin E) (32).

This research received funding of the Faculty of Health at Witten/Herdecke University, Germany, and Helios Center for Research and Innovation by Helios Kliniken GmbH. The funding organizations had no role in study design or conduction, analysis, interpretation of the data, and decision to submit the manuscript for publication. Not any industry or private companies did not finance this study. It is an observational study of purely scientific interest without any interventional testing, including drug discovery or development. Randomization of the subjects or blinding of the study team are not necessary.

All analyzed biomaterials and data involving human participants are in accordance with ethical standards and with the Helsinki declaration (1964) and its later amendments or comparable ethical standards. Ethical approval and later amendment approvals are obtained by the Ethics Committees of Witten/Herdecke University and Ärztekammer Nordrhein, and the study is registered at the German Clinical Trials Register (DRKS). All experiments, including the data extraction and analyses, were and will be obtained pseudonymously. The obtained subject-relevant information and biomaterials were and will be separately coded with study-relevant numbers and codes. All subject-relevant data and experimental results will be filled in a database to perform correlation analyses. With this coding strategy, except the (deputy) study head, nobody may follow retrospectively to patient-sensitive information. All biomaterials were processed according to established internal standard operating procedures and were stored at −80°C or in liquid nitrogen until experimental use. The study recruitment is still ongoing, and the current subject and biomaterial numbers allow first pilot experiments and statistical analyses. The description of the collected data will be done on the basis of statistical parameters. Insofar as the distribution of the data enables, the comparison of the two groups will be carried out using analyses of variance and typical significance tests. Data will be presented as box plots with medians, interquartile ranges, minimum–maximum values or standard deviation, or standard error of the mean. In addition, the data will be presented and analyzed by heat maps, cluster analyses, point clouds, bar, and column charts. Moreover, sequencing results will be normalized within each group, and normalization methods, e.g., DeSeq2, will be performed as previously described by Anders and Huber (33). In addition, metagenomic and proteomic data will be analyzed by professional biostatisticians within our study network. The raw data will be uploaded on separate repository databases, as stated by the journal's requirements. For the experiments, age- and sex-matched stratification will be done between diseased and healthy groups in which each diseased patient will be compared with the same healthy children based on age and sex.

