The inclusion criteria for subjects with asthma are based on international recommendations, including lung function parameters (25), a gestational age over 37 weeks with an inconspicuous peripartal/postnatal period, and presenting an acute asthmatic attack at study enrollment. The definition of subjects with a wheeze is based on previously published data (26–29), including a history of at least two obstructive bronchitis episodes and acute wheezing at study enrollment, as well as an inconspicuous peripartal/postnatal period. Patients (chronic bronchitis and asthmatics) suffering from acute wheezing, respiratory illness, dyspnea, chest tightness, etc. (acute respiratory symptoms) were classified as “exacerbators.” The recruitment of wheezers is clinically and scientifically promising because underlying mechanisms of whether wheezers will develop chronic asthma are not sufficiently understood. Epigenetic signatures/environmental factors are likely to play important roles in disease development and persistence of symptoms (30, 31). We aim to analyze similarities between wheezers and asthmatics to make the diagnosis at the early stages of the disease and to discover potential biomarkers for the clinical routine. Moreover, subjects with no chronic diseases or chronic medication and an inconspicuous neonatal period were classified as healthy controls (age range: 3 months to 65 years of age). The healthy pediatric controls will be age- and sex-matched with diseased children (preschool asthmatics/wheezers and asthmatics). The recruitment of healthy adults will be helpful for correlation analyses of age-dependencies. In the future, we are also planning to include adult asthmatics. This is currently in consideration with the entire study members.

All individuals will be observed on the basis of two follow-up (FU) visits to recognize how the “active” and “non-active” phases are presented and differ, respectively (Figure 2).

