In contrast, there is a large number of advantages to the study. Briefly, there is little data in the literature on infants with chronic bronchitis and adolescents with asthma exacerbation. Questionnaires can be used to identify risk factors that may have potentially led to exacerbation. In addition, impulse oscillometry ensures first lung function volumes in children beyond the age of 2 years, which we additionally collect in the course of the study. Phenotype and endotype comparisons between wheezers and asthmatics can be done, and potential diagnostic and therapeutic schemes can be outlined. The experiments are currently being carried out with the latest technologies and the experimental results. The current biomaterial number of approximately 2.500 samples ensures accurate statistical analyses. Biomarker research is currently one of the most important areas in translational research. Here, we can lay the first foundations with complex experiments and verify their clinical applicability. The large study network from a total of 12 centers offers valid feasibility of the experiments.

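### Healthy controls are to come mostly from children of study-center staff, so diseased-versus-healthy comparisons may partly reflect family background, and age and sex matching does not address this

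*Protocol article*

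**What the plan says.** All of this stands in the Protocol article, mostly under Methods and Analysis.

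- **Source of cases** (text after Table 1): "All patients with typical symptoms requiring study enrollment will be presented at the emergency room of the (affiliated) university children's hospitals".
- **Source of controls** (same paragraph): "Healthy controls will be recruited mostly from children of teammates of the study centers". Community routes follow as an option, "or the following alternatives may be considered for the recruitment of healthy children and adolescents", with examples such as "calls in social platforms, flyers for day-care centers, schools, private practices, social institutions". No minimum share is set for them. The announcements are to be reported to the ethics committees in advance.
- **Matching**: "The healthy pediatric controls will be age- and sex-matched with diseased children". The statistical paragraph repeats the idea for the experiments: "each diseased patient will be compared with the same healthy children based on age and sex".
- **Analysis**: where the distribution allows, "the comparison of the two groups will be carried out using analyses of variance and typical significance tests".
- **Data compared**: Table 1 lists mode of birth, breastfeeding, vaccination and pets, among other items. Aims and Scopes has the swabs of the whole cohort sequenced.
- **Numbers so far**: 62 wheezers, 55 asthmatics and 59 healthy children, adolescents and adults.
- **Limitations** (Advantages and Pitfalls): short observation, follow-up attendance, urban and regional setting, and no adult asthmatics. The source of the controls is not among them.

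**The concern.** A control group should show how common a factor is in the population that gave rise to the cases. Emergency-room patients come from the hospitals' catchment, whereas children of hospital employees come from one occupational group within it. If the two differ in how often children are breastfed, have pets or were born by a given mode, a factor unrelated to asthma will differ between diseased and healthy groups. The same holds for any laboratory measure that varies with such factors.

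Matching on age and sex balances age and sex only. A larger sample does not help either: the bias stays the same size while the standard error shrinks, so a false signal becomes more likely to reach significance. At stake is whether a diseased-versus-healthy difference can be read as a marker of disease.

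**Working it through.** **1. Group sizes.** 62 + 55 + 59 = 176, which agrees with the stated total. Cases: 62 + 55 = 117. Controls: 59, adults included; the number of pediatric controls is not given.

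**2. What has to be assumed.** The article gives no exposure prevalence and no share of staff children among the controls. Both are assumed below and varied.

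- p₀: prevalence in case families and the general catchment, 40%
- p₁: prevalence in staff families, 50% or 60%
- s: share of controls who are staff children, 50%, 70% or 100%
- The factor has no true effect.

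**3. Formulas.**

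- Control prevalence: p_c = s·p₁ + (1 − s)·p₀
- Apparent odds ratio: OR = [p₀/(1 − p₀)] / [p_c/(1 − p_c)]
- SE = √[p₀(1 − p₀)/n_case + p_c(1 − p_c)/n_ctrl], and z = |p₀ − p_c|/SE
- Chance of significance at two-sided 5% (unpooled z-test): Φ(z − 1.96) + Φ(−z − 1.96)

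**4. Two cases in full.**

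- *All 59 controls are staff children, 40% vs 60%.* p_c = 0.60; OR = 0.667/1.5 = 0.44; SE = √(0.24/117 + 0.24/59) = 0.0782; z = 0.20/0.0782 = 2.56; chance = 72%.
- *Half are staff children, 40% vs 50%.* p_c = 0.45; OR = 0.667/0.818 = 0.81; SE = √(0.24/117 + 0.2475/59) = 0.0790; z = 0.05/0.0790 = 0.63; chance = 10%.

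**5. The same calculation over the settings.**

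| Staff share | Controls | 40% vs 50%: OR, chance | 40% vs 60%: OR, chance |
|---|---|---|---|
| 100% | 59 | 0.67, 24% | 0.44, 72% |
| 70% | 59 | 0.75, 14% | 0.57, 42% |
| 50% | 59 | 0.81, 10% | 0.67, 24% |
| 70% | 30 (assumed pediatric only) | 0.75, 11% | 0.57, 28% |

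Cases are 117 in every row. Combining the two milder assumptions (half staff, 30 controls, 40% vs 50%) gives SE = √(0.24/117 + 0.2475/30) = 0.1015, z = 0.49 and a chance of 8%, still above 5%. A pooled z-test changes the top figure from 72% to 71%.

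**6. Effect of a larger sample.** With 70% staff and 40% vs 50%, doubling both groups divides the SE by √2: 0.0792/1.414 = 0.0560, so z = 0.07/0.0560 = 1.25. The chance rises from 14% to 24%.

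**7. Precision without staff children.** If 70% of 59 are staff children, about 0.30 × 59 ≈ 18 controls remain. For a true 60% vs 40% difference, SE = √(0.24/117 + 0.24/18) = 0.124, z = 1.61 and power is about 36%.

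**The case against.** **The effect is not demonstrated.** A reader might infer that group differences *will* reflect staff background. The article does not support that: it reports neither exposure prevalences nor the staff share, so only *may* is justified. This objection stands.

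**The risk-factor analysis may not use controls.** The sentence "Questionnaires can be used to identify risk factors that may have potentially led to exacerbation" names no healthy comparison group and can be read as a question within patients. Elsewhere the questionnaire serves to describe phenotypes, to stratify patients and to correlate with laboratory results. This stands in part, and it would be wrong to conclude that the questionnaire work as a whole is compromised. The statistical paragraph does, however, state a diseased-versus-healthy comparison for the experiments, and the concern applies there and to any questionnaire item compared in the same way.

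**Some supporting arguments fail.** One might cite the Introduction's remark on educational and social level, but that concerns access to diagnosis and treatment, not birth mode, pets or microbiome. One might also argue that staff families carry hospital flora; nothing in the article says so. The point does not rely on either.

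**The large figure is an extreme.** The 72% assumes that every control is a staff child and counts adults among the 59. It also pools wheezers and asthmatics and ignores matching. It is an upper illustration, not an estimate.

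**Adjustment may be planned elsewhere.** Table 1 is a summary, and a fuller protocol or SAP could hold a social-status item, a source variable or covariate adjustment. Their absence from an article is no finding. The finding is the control source that the article does fix, and its omission from the stated limitations.

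**Conclusion.** The concern holds in a limited form. By design, cases and most controls come from different source populations, and what the article states about matching and testing does not deal with that. The exposure is confined to diseased-versus-healthy comparisons. Comparisons between wheezers and asthmatics, and between active and non-active phases in the same subject, do not involve the control source.

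Size and direction are unknown. Under the assumed prevalences, the chance of a false finding for one inert factor is about 10% when half of the controls are staff children, or when 70% are and only 30 controls are pediatric (40% vs 50%). It reaches about 72% when all 59 are staff children (40% vs 60%). If staff and case families do not differ on a factor, and on nothing that influences it, there is no bias for that factor. This is a correctable weakness of a convenience control group in an exploratory cohort, not a reason to discard the design.

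**What to change.** 1. For the remaining recruitment, make the community channels already named under Methods and Analysis the default source of healthy children, with staff children filling empty age and sex cells.
2. Record the recruitment source of every control, including those already enrolled.
3. Repeat each diseased-versus-healthy comparison without staff children as a sensitivity analysis. Compare estimates and confidence intervals with the main result. Do not require significance in the reduced set: with about 18 controls left, power of roughly 36% would suppress most genuine findings.
4. Add the control source to the limitations under Advantages and Pitfalls.

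The cost is one data field, one additional analysis and use of channels for which ethics notification is already foreseen. Control recruitment would be somewhat slower, with recruitment due to close on 31/12/2021, and the sensitivity analysis will be imprecise if few non-staff controls exist. Items 2 to 4 remain possible even if the order of recruitment can no longer be changed.

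### Blinding of the study team is waived because the study is observational, but that reason does not cover masked measurement and analysis of biomarkers

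*Protocol article*

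**What the plan says.** In Methods and Analysis, the paragraph on funding and design says "Randomization of the subjects or blinding of the study team are not necessary". The sentence before it supplies the reason: "It is an observational study of purely scientific interest without any interventional testing, including drug discovery or development". No other reason for the waiver is offered.

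The next paragraph of the same section, on ethics, data handling and statistics, describes the coding:

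- On labelling of data and samples: "The obtained subject-relevant information and biomaterials were and will be separately coded with study-relevant numbers and codes".
- On who can trace a participant: "With this coding strategy, except the (deputy) study head, nobody may follow retrospectively to patient-sensitive information".
- On laboratory work and analysis, the article says only that these are done under pseudonyms.

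On timing and layout of the assays, that paragraph says that samples "were stored at −80°C or in liquid nitrogen until experimental use" and that "the current subject and biomaterial numbers allow first pilot experiments and statistical analyses". On processing of sequencing data it says that "sequencing results will be normalized within each group, and normalization methods, e.g., DeSeq2, will be performed". Advantages and Pitfalls mentions standard operating procedures for handling samples. The article does not say how samples are assigned to plates or runs.

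**The concern.** The waiver is a stated decision and not a detail left out of a condensed article, so it can be judged on its reason. The reason is sound for one half of the sentence only. Nobody randomizes subjects to having asthma. Whether the person at the bench or the analyst knows that a sample comes from a case is a separate matter, and it does not depend on whether the study has an intervention.

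The study compares groups and visits on sequencing, cytokine and cell-culture results (Aims and Scopes; Methods and Analysis). Each involves decisions that knowledge of case status can steer: which samples to repeat, which to exclude at quality control, how to read a culture, which outliers to drop. Such decisions can bias the difference between groups, and a larger sample does not remove that bias.

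The same gap leaves room for a technical artefact. If cases and controls, or baseline and follow-up samples, were assayed in different runs, a run shift could not be separated from the group or visit difference afterwards.

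**Working it through.** **Step 1: does the reason cover the waiver?**

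| Element waived | Reason given | Does the reason suffice? |
|---|---|---|
| Randomization of subjects | Observational, no intervention | Yes |
| Blinding of the study team | Same | No. It does not bear on who measures, checks and analyses samples |

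**Step 2: does the coding supply the masking?** The article says that data and biomaterials carry codes, that experiments and analyses are pseudonymous, and that only the study head or deputy can trace patient-sensitive information. All three statements concern identity. None says that the code, or the information travelling with a sample, withholds group or visit. The sequencing plan points the other way: normalizing within each group requires at least a group label at that step. Unmasked measurement is therefore permitted, though not shown.

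**Step 3: what could run overlap do?** The plan states no alpha, power, effect size or SD, so there is no figure of its own to reproduce. The group counts in Methods and Analysis add up as stated: 62 + 55 + 59 = 176.

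Illustration for 62 wheezers v 59 healthy participants, two-sided 5% z-test, no true difference. The run shift *b*, in SD units, and the split over two runs are assumptions.

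- Standard error: √(1/62 + 1/59) = √0.03308 = 0.1819 SD.
- Net spurious difference: *b* × (share of group 1 in run A − share of group 2 in run A). Full overlap gives *b*. A 75/25 v 25/75 split gives 0.5*b*. Balance gives 0.
- Rejection rate with spurious difference *d*: 1 − Φ(1.96 − *d*/0.1819) + Φ(−1.96 − *d*/0.1819).
- Example, *b* = 0.3, full overlap: 0.3/0.1819 = 1.65, so 1 − Φ(0.31) = 37.8%; the second tail is negligible.
- Example, *b* = 0.3, 75/25 split: 0.15/0.1819 = 0.825, so 1 − Φ(1.135) + Φ(−2.785) = 13.1%.

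| Assumed shift *b* | Balanced | 75/25 v 25/75 | Full overlap |
|---|---|---|---|
| 0.1 SD | 5% | 5.9% | 8.5% |
| 0.2 SD | 5% | 8.5% | 19.6% |
| 0.3 SD | 5% | 13.1% | 37.8% |
| 0.5 SD | 5% | 28.0% | 78.5% |

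The 59 healthy participants include adults, so the age-matched paediatric comparison will be smaller, and the same shift would then inflate the error less. The table describes run overlap only; it does not measure the effect of unblinding.

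**The case against.** The sentence on randomization names subjects, and for a cohort it is correct. It says nothing about samples, plates or runs. A reader might infer that the plan leaves group confounded with assay run. The documents do not support this: the article is silent on run layout, which commonly sits in laboratory procedures or the full protocol. All three groups have been recruited in similar numbers, and nothing shows storage age or run tracking group. Age- and sex-matched comparison, if anything, points away from groups being assayed apart, although it does not guarantee shared runs. Recruitment from January 2018 to the end of 2021, with pilot work on current samples, makes several assay rounds plausible, but rounds do not align with group by themselves. This objection stands.

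A reader might also infer that laboratory staff do know case status. That is not stated either. The study team may mean the clinical team, and the coding may in practice withhold group. This stands in part: the article makes no exception for assay staff or analysts, and it describes the coding only as a protection of identity.

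Finally, Aims and Scopes says that most projects are already done or imminent, so a prospective remedy reaches only what remains. That stands too.

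**Conclusion.** The point holds for masking. The plan declares blinding unnecessary for a reason that does not apply to laboratory measurement, and its coding is not stated to fill the gap. The size of any resulting bias cannot be derived from the documents.

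Confounding of group with run is a possible risk that the article leaves open, not an established fault. The inflation figures are conditional illustrations: at 0.3 SD they run from 5% with balanced runs, through about 13% with a 75/25 v 25/75 split, to 38% with full overlap. Full overlap is the worst case and should not be quoted alone.

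This is a cheap improvement; it is not a defect that invalidates the study.

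**What to change.** Replace the sentence with:

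> Subjects are not randomized. For all assays not yet performed, laboratory staff and analysts work from study codes that do not reveal group or visit until the assay data are locked; where samples are run in batches, diseased and matched healthy samples, and a child's baseline and second-FU samples, are placed in the same run and run is included in the model.

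The lock should fall after repeat runs and quality-control exclusions and before any step that needs a group label, including the within-group normalization if that is kept. The holder of the code key can draw up the run lists, so that nobody at the bench needs the group. If masking is already practised, the present sentence is wrong and only needs correcting.

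**Cost.** Codes already exist, so the work is a run list and withholding the group label. Samples may have to be held until balanced runs can be filled. Completed assays cannot be corrected this way; reports on them should say whether measurement was masked and how groups were spread over runs.
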